#### Monitoring study implementation

The management of unintended harm effects (i.e., a clinically significant increase in mental health symptomatology) and auditing is performed by the supervising clinical psychologist employed for this study, who monitors the clinical evaluations and support group sessions. If necessary, the supervisor can decide to terminate the intervention/clinical assessment and refer the participant to appropriate providers. Trained facilitators offer guidance and assistance to participants experiencing discomfort or adverse effects, ensuring their safety and well-being. Facilitators undergo comprehensive training before the intervention begins to maintain fidelity to the protocol. This training session is conducted by the principal investigator and the project manager designated for the intervention protocol. During this session, facilitators are provided with detailed instructions and guidelines on implementing the intervention protocol effectively. All facilitators adhere to this protocol at the beginning of each session. Protocol changes, if needed, will be communicated to the relevant parties by the PI.

Furthermore, to continually monitor and ensure adherence to the protocol, weekly check-in meetings are held between the project manager and the psychotherapists before each session. These meetings provide an opportunity to review session plans, address any questions or concerns, and reinforce adherence to the protocol. By providing initial training and ongoing support, we aim to equip facilitators with the knowledge and resources they need to deliver the intervention consistently and effectively, thereby enhancing the integrity and reliability of the study outcomes.

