### Outcomes and measures

#### Primary outcomes

The primary outcomes are the levels of depressive symptomatology and anxiety. We assess these outcomes by measuring changes in the total score from baseline to post-intervention. Specifically, we evaluate changes in the total scores of standardized assessment tools for depression and anxiety administered at baseline and post-intervention assessments.

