**Fig. 2 Fig2:**
[figure not shown]
CONSORT flow diagram [36] showing subject allocation to the intervention conditions

The study’s assessment and session timings are as follows: The baseline assessment session is delivered at enrollment, serving as the initial evaluation point. Between the baseline and the first session, approximately 1 to 2 weeks elapse. Subsequent sessions are held weekly thereafter. The mid-intervention assessment occurs after the second session but before the third, either on the day of the third session or 1 day prior. Similarly, the final assessment takes place after the fifth session, either on the same day or 1 day after. Additionally, a follow-up assessment is conducted 3 months after the conclusion of the intervention. In-person sessions are held at one of the NGO collaborators’ offices, providing a conducive environment for participant engagement and support.

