#### Data collection, management, analysis

Eligible participants are assigned a unique identification number and asked to complete the assessment package (primary, secondary, and other outcomes, as well as demographics). The same set of measures are administered mid-intervention (after session 2), final intervention (after session 5), and 3 months after the final session (follow-up assessment).

To ensure high accuracy of data collection, all the measures are completed electronically, via an established survey solution such as QuestionPro, to minimize the risk of missing responses or errors in data entry. The facilitators are responsible for assisting the participants in this process, providing clarifications and explanations when needed.

To promote participant retention and follow-up completion, several strategies are being used. First, the participants receive a clear and complete description of the project, including, but not limited to, information regarding the goals of the support groups, their efficacy, and long-term effects based on evidence. Additionally, the participants will receive reminders about the upcoming session by email or other means to encourage the continuation of the program.

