The improvement in the mental health and well-being scores within and between the groups will be examined using mixed-effects linear regression with a random intercept and slope over time (three assessments: baseline, after session 2, and post-treatment) and fixed effects for treatment assignment. The 3-month follow-up data will be analyzed using linear mixed effects model that incorporates random intercepts for participants and facilitators. Additionally, we may consider including random slopes for time if the data structure warrants it. If ICC analyses will indicate the presence of a hierarchical structure, we will proceed with conducting multilevel analyses. In addition, we will incorporate fixed effects for time and intervention condition and include any necessary covariates. We intend to perform longitudinal analyses in order to ascertain the long-term effects of the intervention. To evaluate changes in outcome measures from the initial measurement to each subsequent assessment, we plan to employ repeated measures ANOVA, where the data is complete, or mixed effects models, where data is incomplete. Moreover, we acknowledge that the linear mixed-effects model allows for the inclusion of covariates (we plan to control for demographics), and this flexibility makes it a robust alternative to repeated measures ANOVA, especially in complex datasets. The use of covariates was taken into account appropriately in the mixed-effects model, which is another reason we plan this approach when dealing with missing or incomplete data. The results of the other measures—demographic variables and therapeutic alliance as potential moderators and mediators—will be examined in an exploratory manner, utilizing regression models or mediation analyses. The error probability and the issue of multiple testing will be addressed either by employing the Bonferroni correction or the false discovery rate correction. Missing data—over 5%—will be handled with multiple imputation methods. Oversight and monitoring of the data collection process is conducted by the principal investigator and the project manager. Check-in regular meetings are held to review the progress of data collection, address any issues that may arise, and ensure compliance with the study protocol and ethical guidelines.

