As with any study investigating mental health variables, there are ethical concerns that need to be addressed. First, the exclusion criteria exclude participants who are diagnosed with an actual mental disorder or pose an imminent danger to themselves or others. Also, potential participants who have scores indicative of posttraumatic stress disorder are also excluded. These people are referred to appropriate services and resources. Second, if a participant’s condition worsens during the intervention, the supervising clinical psychologist can opt to terminate the intervention ahead and make an appropriate referral. Third, since some of the support group topics might be sensitive and could generate delicate disclosures, facilitators are trained to manage this kind of situation and provide the needed support to participants.

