There are, nonetheless, several limitations that must be acknowledged. First, as with many clinical trials testing psychological interventions, psychotherapist blinding is not possible. To minimize possible biases, the principal investigator and the project manager are not involved in any support group sessions. Second, the efficacy of virtual support groups may be influenced by the availability and accessibility of technology (e.g., familiarity with virtual platforms, access to a stable internet connection, etc.). To minimize the risk, participants receive technical assistance through the study and a short introduction on how to use the platform is in place. Third, virtual interventions might face higher rates of attrition and dropout compared to in-person. We monitor and report attrition rates and will conduct sensitivity analyses to assess the impact of dropouts on the results. Nevertheless, we acknowledge that, while Metaverse anonymity comes with several benefits, it can have some limitations for some people (e.g., participants not feeling comfortable not knowing who they are speaking to, maintaining confidentiality, whether the team can know for sure who is accessing the Metaverse platform). To minimize the risks, we have implemented several measures to ensure participant comfort and confidentiality within the Metaverse platform. Firstly, participants have the opportunity to meet the trainer before the sessions, either online or in-person, providing them with the opportunity to establish a rapport and familiarize themselves with the facilitator. Secondly, to ensure that the team can verify the identity of participants accessing the Metaverse platform, each participant is given a unique access code. This code is exclusively available to the participant and serves as a secure identifier when accessing the platform. By providing participants with individualized access codes, we can accurately track and monitor participation while maintaining confidentiality and ensuring that only registered participants have access to the sessions.

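### The safety-stop rule allows a worsening participant's clinical assessment to be ended, and the protocol does not keep the PHQ-9 and GAD-7 going afterwards; a cheap improvement, with small expected bias

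*Protocol article*

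**What the plan says.** Monitoring study implementation defines unintended harm as a clinically significant rise in symptoms. It gives the response to a supervising clinical psychologist "who monitors the clinical evaluations and support group sessions". Where necessary, "the supervisor can decide to terminate the intervention/clinical assessment and refer the participant to appropriate providers".

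Ethics and dissemination returns to a participant who gets worse during the intervention: "the supervising clinical psychologist can opt to terminate the intervention ahead and make an appropriate referral". It does not mention assessments.

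Primary outcomes defines the endpoint as the change from baseline to post-intervention in total scores on "standardized assessment tools for depression and anxiety administered at baseline and post-intervention assessments". These are the PHQ-9 and GAD-7. Data collection, management, analysis has the same set of measures completed electronically at every time point. It makes no exception for stopped participants and gives no assurance about them. Participant timeline ties the last on-treatment measurement to the sessions: "the final assessment takes place after the fifth session, either on the same day or 1 day after".

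For incomplete data, the plan uses mixed models, and missing data above 5% "will be handled with multiple imputation methods". The Discussion adds that the team "will conduct sensitivity analyses to assess the impact of dropouts on the results".

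**The concern.** The trigger for a stop, rising symptoms, is close to what the primary outcome measures. If the stop also ends the questionnaires, a final score is missing because the participant got worse. Imputation from baseline and mid-intervention scores recovers worsening already visible at mid-intervention. It does not fully recover worsening that arises during sessions 3 to 5 and is never scored.

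Two things are at stake. The first is the comparison with the waitlist. The supervisor observes sessions and waitlist participants have none, so worsening between assessments is more likely to be noticed in the active arms. That difference is an inference from the design, not something the article states. The second is the harm evidence itself. The rationale section says it is unclear whether online support groups have unintended side effects, and the participants who would show this may have no final score.

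**Working it through.** **Reading the text.** The sentence before the rule pairs clinical evaluations with support group sessions; the rule pairs the intervention with clinical assessment. This supports a narrow reading, in which only an evaluation in progress is ended. On the other side, Primary outcomes describes the PHQ-9 and GAD-7 as assessment tools given at assessments, and the article uses assessment for the scheduled measurement occasions throughout. Apart from screening, these are the only assessments it describes. The broad reading is therefore plausible but not established.

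**The plan's own figure.** The sample size of 45 is not in dispute; it is used here to set the scale. For the within-between interaction, λ = f²·N·m·ε/(1−ρ). With f = 0.25, N = 45 and m = 4 from the Sample size section, and ρ = 0.5 and ε = 1 assumed, λ = 0.0625 × 45 × 4 / 0.5 = 22.5, with df 6 and 126. Power is 0.955, so 45 reproduces. Loss of numbers alone matters little: 42 or 40 complete participants give 0.939 or 0.925. The question is bias.

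**Bias inputs, all assumed.** PHQ-9 SD 5; correlation r between scores 0.5 or 0.7; true benefit 0 or 2 points, with 40% reached at mid-intervention and 80% at an unrecorded state between mid and post. A participant whose trigger score is at least 5 points above baseline is stopped with probability 0.5 or 1 and loses the post score. The missing score is predicted by within-arm regression on baseline and mid scores. Bias is the estimated minus the full-data difference in change, active minus waitlist; negative means towards benefit. The simulation uses 2,000,000 per arm.

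**Number of stops.** The SD of the difference between two scores is 5·√(2(1−r)), which is 5.00 at r = 0.5 and 3.87 at r = 0.7.
- Highest: P(Z ≥ 5/5.00) = 0.159, and × 15 = 2.4 per arm.
- Lowest: P(Z ≥ (5 + 0.8 × 2)/3.87) = 0.044, and × 0.5 × 15 = 0.3 per arm.

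**Bias when only the active arms are stopped, on the unrecorded state** (stop probability 0.5 / 1):

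| r | True benefit | Equal correlations | Unrecorded–post correlation raised |
|---|---|---|---|
| 0.5 | 0 | −0.12 / −0.27 | −0.29 / −0.69 (raised to 0.75) |
| 0.5 | 2 | −0.08 / −0.17 | −0.19 / −0.42 (raised to 0.75) |
| 0.7 | 0 | −0.08 / −0.17 | −0.17 / −0.37 (raised to 0.85) |
| 0.7 | 2 | −0.04 / −0.08 | −0.09 / −0.18 (raised to 0.85) |

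**Other settings.**
- The recorded mid score is the trigger: 0.00 throughout.
- The waitlist is stopped by the same rule: 0.00 with no true effect. With a 2-point benefit, +0.04 to +0.10, or up to +0.26 with the raised correlation, against benefit.
- The missing final score is itself the trigger, active arms only: −0.11 to −1.10. This is an extreme bound, because no session remains after that score.

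**Scale.** The standard error of the difference in change with 45/3 = 15 per arm is √(2 × 2 × 25 × (1−r)/15), which is 1.83 at r = 0.5 and 1.41 at r = 0.7. The largest equal-correlation bias is 0.27/5 = 0.05 SD, or 0.27/1.83 = 0.15 standard errors.

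**The case against.** A reader might infer that the two sections contradict each other. They do not. The Ethics and dissemination sentence is permissive and silent on assessments. It neither confines the psychologist to ending the intervention nor promises that questionnaires continue. One section names one permitted action and the other names two.

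A reader might also infer that the trial plans to discard the outcomes of participants who worsen. The documents do not support that either. The narrow reading fits the preceding sentence well, the phrase clinical assessment is never applied to the questionnaires elsewhere, stopping is discretionary, and the schedule is given without exceptions.

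The remaining objections concern size and scope. Bias towards benefit needs four things together: the broad reading, use of the discretion, stops mainly in the active arms, and worsening not yet scored. The stop frequency is assumed, and generously so: with no true effect and r = 0.5, a 5-point rise is a one-SD fluctuation. Discretion to stop questioning a distressed refugee is also a sound safety choice. All of this stands, and it is why the point is minor.

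The argument that this is only a detail left to a fuller document does not stand. The article states a conduct rule that permits assessment to end, and no later analysis plan can restore scores that were never collected.

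**Conclusion.** The point holds as a cheap improvement. The rule as written can cost final PHQ-9 and GAD-7 scores because of worsening, provided clinical assessment includes those questionnaires. The planned mixed models, imputation and dropout sensitivity analyses reduce the resulting bias but do not fully remove it when the worsening is unrecorded. The expected size is small against the trial's own sampling error. It rests on assumed SD, correlations and stop rates, and its direction depends on which arms are stopped. Between the two active arms, which share the rule, no bias is expected if effects and stops are alike. The firmer reason to act is that participants with a safety event should not lack the score that would show the harm.

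**What to change.** In Monitoring study implementation, state that a safety stop ends the sessions and any interview in progress. State also that the remaining electronic PHQ-9 and GAD-7 are still offered at their scheduled times in all arms, unless the participant declines or withdraws, or the supervisor records that completing them would be harmful. A matching clause in Ethics and dissemination would keep the two sections in step.

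This takes one or two sentences and changes no sample size. The cost is a few extra short surveys offered to referred participants and a recorded reason whenever assessment is ended. Clinical discretion is kept, but ending assessment becomes a documented exception.

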#### Ethics and dissemination

The study has been approved by the ethics committee of the University of Bucharest, Romania. Individuals expressing their interest in participating in the study access a link to a QuestionPro-type form, where they can find the informed consent as well as the instruments. The informed consent sheet includes information about the project coordinators, project purpose, and objectives, as well as information about the results and how they will be used, information about the participants role in the project, and what their rights are. It is specified that participation is entirely voluntary, and participants can exit the study at any time/stage without any consequences. Information about confidentiality and its preservation are also included as follows: all information received from participants will be treated as strictly confidential, in accordance with GDPR, the institution’s rules, and the ethical norms governing high-quality research worldwide; information recorded on paper or entered into the computer will be identified only by a code number; a list of participants’ names and codes will be kept separately and securely.

To enhance understanding and address any questions or concerns, our facilitators personally engage with each participant through phone calls or in-person meetings to explain the consent process in detail and take the consent from the participants.

Enrollment in the study takes place after participants agree, by checking boxes in the form, to the following aspects:That they have understood and received all necessary information to decide knowingly if they want to participateVoluntary agreement to enroll in the studyAgreement regarding the use of data in the study: the understanding that the data will only be used for research purposes, in accordance with the informed consent form. Interested individuals can address further questions either to the project’s email address, the coordinator, or through the informed consent form

As with any study investigating mental health variables, there are ethical concerns that need to be addressed. First, the exclusion criteria exclude participants who are diagnosed with an actual mental disorder or pose an imminent danger to themselves or others. Also, potential participants who have scores indicative of posttraumatic stress disorder are also excluded. These people are referred to appropriate services and resources. Second, if a participant’s condition worsens during the intervention, the supervising clinical psychologist can opt to terminate the intervention ahead and make an appropriate referral. Third, since some of the support group topics might be sensitive and could generate delicate disclosures, facilitators are trained to manage this kind of situation and provide the needed support to participants.

#### Dissemination policy

The research team intends to publish the trial results in a peer-reviewed journal and also present the findings at conferences.

## Discussion

This protocol outlines a randomized clinical trial conducted to assess the efficacy of virtual support groups (i.e., groups meeting in the Metaverse) for Ukrainian refugees. The study aims to examine the effects of these virtual support groups on the mental health, social integration, and overall well-being of displaced Ukrainian refugees. Utilizing immersive technologies, this trial seeks to provide a safe, accessible, and culturally sensitive virtual environment for Ukrainian refugees to connect, share experiences, and receive support despite physical distance and geographical constraints.

To our knowledge, this is the first attempt to assess the efficacy of virtual support groups for Ukrainian refugees. The study can thus provide essential insights into the potential benefits of using the Metaverse in delivering support group sessions. This randomized trial will contribute to the development of targeted, scalable interventions and policies to promote the well-being of Ukrainian refugees.

There are, nonetheless, several limitations that must be acknowledged. First, as with many clinical trials testing psychological interventions, psychotherapist blinding is not possible. To minimize possible biases, the principal investigator and the project manager are not involved in any support group sessions. Second, the efficacy of virtual support groups may be influenced by the availability and accessibility of technology (e.g., familiarity with virtual platforms, access to a stable internet connection, etc.). To minimize the risk, participants receive technical assistance through the study and a short introduction on how to use the platform is in place. Third, virtual interventions might face higher rates of attrition and dropout compared to in-person. We monitor and report attrition rates and will conduct sensitivity analyses to assess the impact of dropouts on the results. Nevertheless, we acknowledge that, while Metaverse anonymity comes with several benefits, it can have some limitations for some people (e.g., participants not feeling comfortable not knowing who they are speaking to, maintaining confidentiality, whether the team can know for sure who is accessing the Metaverse platform). To minimize the risks, we have implemented several measures to ensure participant comfort and confidentiality within the Metaverse platform. Firstly, participants have the opportunity to meet the trainer before the sessions, either online or in-person, providing them with the opportunity to establish a rapport and familiarize themselves with the facilitator. Secondly, to ensure that the team can verify the identity of participants accessing the Metaverse platform, each participant is given a unique access code. This code is exclusively available to the participant and serves as a secure identifier when accessing the platform. By providing participants with individualized access codes, we can accurately track and monitor participation while maintaining confidentiality and ensuring that only registered participants have access to the sessions.

